##### Clinical disease

The primary case definition for the trial was chosen with the following considerations in mind. It was important that it represents true cases of malaria at the more severe end of the disease spectrum. Therefore, cases contributing to the primary case definition are children who have been judged to be ill by their parents and brought for treatment to their local hospital or health facility. These cases are defined as febrile ( 37.5°C) with a parasitaemia level above a cut off value. In malaria endemic areas parasitaemia is common in the absence of symptoms. This means that sick children with a range of conditions may have coincidental parasitaemia, but that this is not the cause of the illness. Methodology proposed by T. Smith models the relationship between parasite density and fever in a population and defines a threshold above which the parasitaemia is likely to be the cause of the fever. In this population this was determined as 2500 parasites per µl and using this definition, the case definition has been estimated to be 91% specific and 95% sensitive[[17]](#endnote-18). The high specificity will ensure that the estimate of effect is not a significant underestimate of the true vaccine efficacy.

The primary endpoint is time to first clinical attack, which is a suitable method for assessing the efficacy of a vaccine inducing partial immunity to malaria. This type of vaccine, which gives partial protection to most vaccinees (rather than a vaccine that protects completely a proportion of the population) cannot be assessed using a comparison of the proportions of people affected because over time, as progressively more subjects experience their first attack, the measured efficacy will trend to zero.

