In addition to the primary objective, data will be analyzed to determine the time to first clinical presentation of a haematocrit below 25%. The average attack rate for anaemia (as defined as a haematocrit of less than 25%) at the Manhiça District Hospital between 1998 to 2001 was 6% over 6 months. A sample size of 704 per group will achieve 68% power to detect a difference of 0.03 between the null hypothesis that both group proportions are 0.06 and the alternative hypothesis that the proportion in the RTS,S/AS02A group is 0.03 using a two-sided log rank test with a significance level of 0.05.

(Sample size calculations were performed using NCSS trial and Pass 2000).

### Cohort 2

The overall aims for Cohort 2 of the study are two fold:

- to assess the efficacy of the RTS,S/AS02A malaria candidate vaccine in delaying time to first asexual falciparum infection.
- to compare the humoral response for anti-HBs antibodies induced by the RTS,S/AS02A malaria candidate vaccine with the humoral response to Engerix-B™ (hepatitis B vaccine).

Table 6 presents the sample sizes required to detect a vaccine efficacy of 50% in the prevention of new infections. A study with a sample size of ***166*** ~~142~~ evaluable subjects per group will have an ***86*** ~~80~~% power to detect a lower confidence interval of 20%. The age distribution of Cohort 2 will reflect that of Cohort 1.

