**(Amended January 17, 2003)**

Table 6: Sample size to establish the lower limit of the 95% CI of vaccine efficacy in Cohort 2

| **Number of malaria infected subjects in Control Vaccine Group** | **Number of malaria infected subjects in Malaria Vaccine Group** | **Lower limit of 95% CI for vaccine efficacy** | **Number of subjects per group** |
| --- | --- | --- | --- |
| ~~139~~ ***162*** | ~~69~~ ***81*** | 30% | ~~277~~ ***325*** |
| ~~95~~ ***112*** | ~~48~~ ***56*** | 25% | ~~191~~ ***224*** |
| ~~71~~ ***83*** | ~~36~~ ***42*** | 20% | ~~142~~ ***166*** |
| ~~45~~ ***53*** | ~~23~~ ***27*** | 10% | ~~91~~ ***106*** |
| ~~38~~ ***45*** | ~~19~~ ***22*** | 5% | ~~76~~ ***89*** |
| ~~36~~ ***42*** | ~~18~~ ***21*** | 3% | ~~71~~ ***84*** |
| ~~33~~ ***39*** | ~~17~~ ***19*** | 0.5% | ~~66~~ ***78*** |

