##### Cohort 2: secondary endpoint

Time to first infection of asexual stage *P. falciparum* parasites will be examined using Kaplan-Meier curves for both groups and these will be compared using the log-rank test or Wilcoxon test. Cox regression will be used to assess the significance of the group effect and the vaccine efficacy (defined as 1-R, where R is the hazard ratio [RTS,S/AS02A:control vaccine]) will be estimated from the hazard ratio of the RTS,S/AS02A group versus the Control group (with 95% CI) adjusting for prognostic/stratifying factors (see section 10.7.2.2.7).

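### Cohort 2's 86% power is for a risk ratio of 0.5, but efficacy will be estimated as 1 minus the hazard ratio; at 50% efficacy on that scale the power is about 75%

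*Supplement*

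**What the plan says.** **Sample size.** Section 10.6.2 introduces the Cohort 2 infection calculation with "Table 6 presents the sample sizes required to detect a vaccine efficacy of 50% in the prevention of new infections". It claims 86% power for a lower limit of 20% with 166 evaluable subjects per group. The table's caption is "Table 6: Sample size to establish the lower limit of the 95% CI of vaccine efficacy in Cohort 2". Its 20% row has 83 infected controls and 42 infected vaccinees out of 166 each. The other rows keep the same 50% versus 25% pattern. The text states neither the 50% control risk nor the scale of the efficacy.

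**Analysis.** Section 10.7.2.2.6 plans Kaplan-Meier curves and Cox regression for time to first infection, with "vaccine efficacy (defined as 1-R, where R is the hazard ratio [RTS,S/AS02A:control vaccine]) will be estimated from the hazard ratio".

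**The protocol's own view of proportions.** Section 1.2.2.1.1, arguing for the primary endpoint, says that a partially protective vaccine "cannot be assessed using a comparison of the proportions of people affected because over time" measured efficacy drifts towards zero as first events accumulate.

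**Cohort 1.** Section 10.6.1 uses a relative-risk sample size method and then repeats the calculation by simulation, with efficacy as a hazard reduction and a Cox analysis. No such check is given for Cohort 2. The same section states for anaemia: "A sample size of 704 per group will achieve 68% power to detect a difference of 0.03 between the null hypothesis" of 6% in both groups and 3% in the vaccine group, using a two-sided log-rank test at 0.05.

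**The concern.** The same words, a vaccine efficacy of 50%, mean a halved cumulative risk in the sample size section and a halved hazard in the analysis section. When events are rare the difference is small. When half the controls have the event it is not, and a power worked out on one scale does not carry over to an analysis on the other. A reader who takes section 10.6.2 at face value will expect about a 1 in 7 chance that the Cohort 2 interval fails to exclude 20% when the hazard is truly halved. On the planned analysis the chance is about 1 in 4. Cohort 2 is there to help separate an effect on infection from an effect on disease alone, so its precision should be described correctly.

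**Working it through.** **Inputs.** Per-group size 166; 83/166 = 50% and 42/166 = 25% infected (Table 6); two-sided 95% interval, z = 1.96; limit to exclude 20%, a ratio of 0.80; efficacy = 1 − hazard ratio (section 10.7.2.2.6); 1:1 allocation.

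**1. Reproducing 86%.** Log relative risk with p1 = 0.50, p2 = 0.25:
- SE = √[(1−0.50)/(166×0.50) + (1−0.25)/(166×0.25)] = √(4/166) = 0.1552
- ln(0.80/0.50)/0.1552 − 1.96 = 0.470/0.1552 − 1.96 = 1.07
- Power = Φ(1.07) = 85.7%

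The same formula gives 85.7% to 86.0% for every row of Table 6. At 80% power it also returns every Table 5 sample size to within one subject. The stated 86% is therefore a risk-ratio power.

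**2. The same scenario as a hazard ratio.** Under proportional hazards, HR = ln(1−0.25)/ln(1−0.50) = 0.415. That is an efficacy of 58%, not 50%.

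**3. A true hazard ratio of 0.5, control risk 50%.**
- Vaccine-group risk = 1 − 0.5^0.5 = 0.293; 166 × 0.293 = 48.6, about 49 infected
- Expected events = 83 + 48.6 = 131.6
- Wald: SE = √(1/83 + 1/48.6) = 0.1806; 0.470/0.1806 − 1.96 = 0.64; power 74.0%
- Schoenfeld: √(131.6/4) × ln(1.6) − 1.96 = 0.74; power 76.9%
- 10,000 simulated trials analysed by Cox regression: 75.4%

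Grouping infection times to the scheduled visits leaves the simulated power at about 74% to 75%. The lower limit reached with 80% power is 1 − 0.5 × exp(2.80 × SE): 17% with the Wald SE, and 19% with the Schoenfeld SE of 2/√131.6 = 0.174.

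**4. Cox power if 50% versus 25% were true (HR 0.415).** Wald 93.2%, Schoenfeld 95.6%, simulation 94.4%.

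**5. Dependence on the control risk, HR 0.5, 166 per group (Wald to Schoenfeld).**

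| Control risk | Power to exclude 20% |
|---|---|
| 40% | 63% to 67% |
| 50% | 74% to 77% |
| 60% | 82% to 85% |
| 70% | 89% to 90% |

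**6. Why Cohort 1 is little affected.** At an 11% attack rate, HR 0.5 gives 1 − 0.89^0.5 = 5.7% against the 5.5% of a halved risk, so the two scales nearly agree.

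**7. Anaemia.** Inputs as stated: 704 per group, 6% versus 3%, two-sided log-rank at 0.05.
- HR = ln(0.97)/ln(0.94) = 0.492; events = 704 × 0.09 = 63.4
- Freedman: √63.4 × (1−0.492)/(1+0.492) − 1.96 = 0.75; power 77%
- Schoenfeld: √(63.4/4) × 0.709 − 1.96 = 0.86; power 81%

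The stated 68% is about 9 to 13 points lower.

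**The case against.** **The 86% is not a slip of arithmetic.** This stands. It is correct for the counts printed in Table 6. The fault is that the counts and the planned estimate use different scales and the text does not say so.

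**Under the printed counts the Cox analysis does better than 86%, so the figure is conservative.** True for those counts, but they are then an efficacy of 58% on the planned scale, and the text says 50%. Relabelling alone would not rescue the figure, because the matching power is about 94%.

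**Little hangs on it.** Much of this stands. Time to infection is secondary, and the development decision rests on clinical disease in Cohort 1. Amendment 2 raised Cohort 2 to 416 to protect the hepatitis B comparison, not the infection endpoint. A reader might infer that missing the 20% limit would count as a weak infection effect or change a decision. No section attaches any such rule to it. With HR 0.5 the power for a lower limit above zero is still about 97% (0.693/0.1806 − 1.96 = 1.88).

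**The 75% is itself conditional.** It is. It uses Table 6's own control risk, and a different attack rate could move the power by as much as the change of scale does. The simulations also assume constant hazards and ignore the time deducted after malaria treatment. That is a reason to state the assumption, not to keep a figure from another scale.

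**Anaemia.** A reader might infer that 704 was reduced a second time for losses, since about 563 per group (704 × 0.8) gives about 68%. The documents do not show this. Two proportions at 704 per group with a two-sided level of 0.025 also give about 68%, so the origin of the figure is unknown.

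**Conclusion.** The point holds. The 86% in section 10.6.2 is not the power of the planned Cox analysis at 50% efficacy. At Table 6's 50% control risk and a true hazard ratio of 0.5, the power to exclude 20% is about 75%, roughly 10 points lower. This rests on proportional hazards, 166 evaluable children per group and the 50% control risk. The anaemia power of 68% does not match its stated inputs, which give about 77% to 81%; that figure errs on the cautious side. Neither correction affects the primary endpoint, the analysis methods or the number of children.

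**What to change.** 1. Restate Table 6 on the hazard-ratio scale. Keep the group sizes and set the vaccine-group counts to n × 0.293: 95, 66, 49, 31, 26, 25 and 23 in place of 81, 56, 42, 27, 22, 21 and 19. Give the power for the 20% limit at 166 per group as about 75%. Alternatively, keep 83 versus 42, label it as an efficacy (1 − hazard ratio) of about 58%, and give its Cox power of about 94%.
2. State in the text of section 10.6.2 that a 50% control infection risk is assumed, and show the power at one lower and one higher risk. A short Cox simulation like the one reported for Cohort 1 would serve.
3. Recompute the anaemia power in section 10.6.1 from its stated inputs (about 77% to 81%), naming the method, or state the inputs that give 68%.

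The cost is a few lines of text and one table. The Cohort 2 figure at 50% efficacy becomes less favourable, the anaemia figure more so.

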**(Amended January 17, 2003)**

Table 6: Sample size to establish the lower limit of the 95% CI of vaccine efficacy in Cohort 2

| **Number of malaria infected subjects in Control Vaccine Group** | **Number of malaria infected subjects in Malaria Vaccine Group** | **Lower limit of 95% CI for vaccine efficacy** | **Number of subjects per group** |
| --- | --- | --- | --- |
| ~~139~~ ***162*** | ~~69~~ ***81*** | 30% | ~~277~~ ***325*** |
| ~~95~~ ***112*** | ~~48~~ ***56*** | 25% | ~~191~~ ***224*** |
| ~~71~~ ***83*** | ~~36~~ ***42*** | 20% | ~~142~~ ***166*** |
| ~~45~~ ***53*** | ~~23~~ ***27*** | 10% | ~~91~~ ***106*** |
| ~~38~~ ***45*** | ~~19~~ ***22*** | 5% | ~~76~~ ***89*** |
| ~~36~~ ***42*** | ~~18~~ ***21*** | 3% | ~~71~~ ***84*** |
| ~~33~~ ***39*** | ~~17~~ ***19*** | 0.5% | ~~66~~ ***78*** |

**(Amended January 17, 2003)**

This study will compare the immunogenicity of a licensed hepatitis B vaccine (Engerix-B) and RTS,S/AS02A. A non-inferiority approach will be used to calculate the power of the study for the comparison of seroprotection rates and geometric mean titres of anti-HBs antibodies. From census information gathered by CISM, approximately ***25%*** ~~12.5%~~ of the population will be less than ***24*** ~~18~~ months of age. Therefore the assessment of the anti-HBs antibody immune response will be based on approximately 248 evaluable subjects (124 subjects per group). This sample size will have ***89%*** ~~95%~~ power at a ***2.5%*** ~~5%~~ significance level using a one-sided equivalence test of proportions when the proportion that are seroprotected in the control group (subjects vaccinated with Engerix-B™) is at least 0.95 and the proportion in the RTS,S/AS02A group (subjects of ***24*** ~~18~~ months of age or more) is 0.95 and the maximum allowable difference between these proportions that still results in equivalence (the range of equivalence) is 0.10 (PASS 2000,one sided equivalence test of proportions, alpha = ***2.5%*** ~~5%~~).
**(Amended January 17, 2003)**

Similarly this sample size will provide 99% power to demonstrate at 10% significance level using an equivalence of means test, that the lower limit of a two sided 90% confidence interval on the GMT ratio of anti-HBs antibodies (RTS,S/AS02A vaccine group over Engerix-B™ vaccine group ) is greater than 0.5 (2 fold decrease). (PASS 2000, equivalence of means, alpha = 10%). The standard deviation used for this calculation was 0.591 ***(computed on log base 10 transformed tires)*** and was derived from a GSK Biologicals study (DTPw-HBV-033) in which three doses of vaccine were administered to each subject at 3 months, 4 months and 5 months of age[[35]](#endnote-36).
**(Amended January 17, 2003)**

The 248 subjects available for tests of non-inferiority will include both seronegative and seropositive subjects to the HBsAg at baseline. Table 7 shows the power to meet the non-inferiority criterion if the number of **seronegative only** subjects in the non-inferiority cohort varies. All parameters used for the initial calculations above remain constant except for sample size. All calculations used Pass 2000.

Table 7 : Power to achieve non-inferiority criterion for seroprotection and GMT ratio given the availability of seronegative only subjects in the non-inferiority cohort (124 per group)

| Number of seronegative subjects | Percentage of seronegative subjects in non-inferiority cohort1 | Power to achieve non-inferiority criterion for: | |
| --- | --- | --- | --- |
| Seroprotection | GMT ratio |
| 112 | 90 | 92 | 99 |
| 99 | 80 | 89 | 98 |
| 87 | 70 | 85 | 96 |

1: non-inferiority cohort = 124 subjects from cohort 2  ***24*** ~~18~~ months of age who receive either RTS,S/AS02A or Engerix-B™. Computed using PASS 2000. **(Amended January 17, 2003)**

Allowing for approximately 20% of subjects who may drop out or who may not be evaluable for analysis, ***416*** ~~356~~ subjects are needed for the analysis of this study cohort objective.

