| - Amendment of the methodology for assessment of the non-inferiority of RTS,S/AS02A against Engerix-B™ to replace the a lower limit of a 90% two-sided confidence interval with the lower limit of a 95% two-sided confidence interval, as recommended by the FDA (see section 10.7.4). - Adjustment of the sample size for the non-inferiority comparison of RTS,S/AS02A against Engerix-B™ for a one-sided alpha of 0.025 instead of 0.05 (see section 10.6.2). - Addition of the period from day 0 (first vaccination) to month 21 to the intention to treat analysis of vaccine efficacy (sections 10.7.2.1 and 10.7.2.2.9).  1. In addition, the principal investigator (PI) has requested two changes to the study protocol:  - The screening period will be extended from the current 35 days prior to first vaccination to 90 days prior to first vaccination (Synopsis and sections 3, 5.3, 5.4, 5.5, 5.6 and 5.8.4). - The measurement of spleen size, body weight and height or length will be performed at screening (Clinic visit 1) and not on day 0 (Clinic visit 2), for both cohorts, for logistical reasons. The measurement of body weight and height or length at screening will facilitate the determination of the exclusion criterion for severe malnutrition (sections 5.3, 5.4, 5.5 and 5.6).  1. The DSMB commented, in their review of the study protocol, on the inappropriateness of the requirement for reporting congenital abnormalities in offspring after cessation of the study, in view of the characteristics of the study population (children of 1 to 4 years of age). This part of the protocol has been revised to provide clearer guidance for reporting serious adverse events after study conclusion (see section 8.5.2). 2. For parasite genotyping analysis, in Appendix F it is stated that each time a malaria smear is obtained, whether for routine collections or to evaluate clinical symptoms, a few drops of blood will be collected onto filter paper for analysis.  The collection period for blood samples for parasite genotyping analysis was omitted from the text in Appendix F. The appendix now states that filter paper should be collected for the surveillance period for primary and secondary endpoints (day 90 up to and including day 256).  To be consistent, the text in section 1.2.2.2 has been corrected to remove the specification stating which parasites will be characterised. Clinic visit 4 (day 60) in Cohort 2 does not specify that whole blood will be collected onto filter paper for parasite genotyping analysis even though a finger prick blood sample will be taken for a blood film for parasitaemia determination. This inconsistency has been corrected and whole blood will now be taken on filter paper at Clinic visit 4 in Cohort 2 (see sections 5.5, 5.6 and 5.8.3). This will not entail any additional blood sampling from subjects. There will be sufficient blood taken for the blood film to prepare the blood spot necessary for the analysis of the parasite genotype. These filter paper samples will be stored and analysed as the other samples taken for parasite genotyping in Cohort 1 and 2. 3. The contact details of the local GSK monitor and the Study Monitor have been changed to reflect current appointments (see Title pages, section 8.5.2 and Appendices D and E). 4. By omission, the Screening sampling time point was not specified in Appendix G (Vaccine Supplies, Packaging and Accountability). This has been corrected. | | | | |

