**(Amended January 17, 2003)**

For each treatment group in Cohort 2, the seroprotection rate for anti-HBs antibodies (proportion of subjects with anti-HBs antibody titres of  10 mIU/ml) and its 95% CI will be tabulated by vaccine dose. GMTs for anti-HBs antibodies measured in mIU/ml with 95% CI will be calculated for each group at each time point when a serology sample is available. Reverse cumulative curves will be plotted for anti-HBs antibody titres measured at month 8½. GMTs for anti-RF1-like antibodies, measured in EL.U/ml, with 95% CI will be calculated for each group at each time point when serology sample is available. For GMT calculations, antibody titres below the cut-off of the assay (10 mIU/ml) will be given an arbitrary value of half the cut-off for the purpose of calculating the GMTs.

Number and percentage, with 95% CI, of children of 18 months of age or more at first vaccination with seroprotective levels of anti-HBs antibodies (seroprotective levels are defined as anti-HBs titres of 10 mIU/l or greater) at day 90 will be computed.

***This study will compare the immunogenicity of (Engerix-B™) and RTS,S/AS02A. A non-inferiority approach will be used to calculate the power of the study for the comparison of seroprotection rates and geometric mean titres of anti-HBs antibodies. From census information gathered by CISM, approximately 25% of the population will be less than 24 months of age. Therefore the assessment of the anti-HBs antibody immune response will be based on approximately 248 evaluable subjects (124 subjects per group). This sample size will have 89% power at a 2.5% significance level using a one-sided equivalence test of proportions when the proportion that are seroprotected in the control group (subjects vaccinated with Engerix-B™) is at least 0.95 and the proportion in the RTS,S/AS02A group (subjects of 24 months of age or more) is 0.95 and the maximum allowable difference between these proportions that still results in equivalence (the range of equivalence) is 0.10 (PASS 2000, one sided equivalence test of proportions, alpha = 2.5%).***~~The difference between seroprotection rates at month 4 for anti-HBs antibodies between both groups will be calculated as well as the 90% CI around these difference. If the lower limit of the two-sided 90% CI (corresponding to a one-sided 95% CI) is greater than –10%, non-inferiority of RTS,S/AS02A compared to Engerix-B™ will have been demonstrated in this study.~~

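### Table 7's seroprotection powers (92/89/85%) were left at the superseded one-sided 5% level; at the current 2.5% they should read about 85/80/74%

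*Supplement*

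**What the plan says.** Cohort 2 compares the anti-HBs response to RTS,S/AS02A with that to Engerix-B in children aged 24 months or more at first vaccination. Section 10.6.2 of the protocol (Amendment 2, January 17, 2003) assumes 124 evaluable subjects per group, a seroprotection rate of 0.95 in both groups and a margin of 0.10. Section 10.7.4 repeats the result: "This sample size will have 89% power at a 2.5% significance level using a one-sided equivalence test of proportions". Amendment 2's list of changes says the non-inferiority comparison was adjusted "for a one-sided alpha of 0.025 instead of 0.05 (see section 10.6.2". In the marked-up text of 10.6.2, alpha goes from 5% to 2.5% and power from 95% to 89%.

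Table 7 extends this to baseline-seronegative subjects, taken as 90%, 80% or 70% of the 124 per group. It is introduced with "All parameters used for the initial calculations above remain constant except for sample size". Its entries are:

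| Seronegative per group | Share of 124 | Seroprotection power | GMT power |
|---|---|---|---|
| 112 | 90% | 92% | 99% |
| 99 | 80% | 89% | 98% |
| 87 | 70% | 85% | 96% |

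The only change marked in Table 7 is the age cut-off in its footnote. None of the powers is marked as revised.

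**The concern.** The text and the table cannot both be right. If only the sample size differs, power at 112 per group must be below the 89% given for 124, and power at 99 per group cannot equal it.

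Table 7 is the only place where the protocol states power for the seronegative-only comparison, and section 10.7.4 commits to that comparison alongside the one in all subjects. A reader would conclude that it keeps at least 85% power even if only 70% of subjects are seronegative. At the level now specified that is not so. A failure to show non-inferiority in that subset would then be read against a stated power that is too high.

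**Working it through.** **Inputs** (section 10.6.2): rate 0.95 in each group, true difference 0, margin 0.10, one-sided alpha 2.5% (formerly 5%), n = 124 per group. The Table 7 counts are per group: 0.90 × 124 = 111.6, 0.80 × 124 = 99.2 and 0.70 × 124 = 86.8, which round to 112, 99 and 87.

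**Method.** Farrington-Manning non-inferiority test for two proportions, normal approximation:

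power = Φ[(0.10 − z·s0) / s1]

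- s1² = 2 × 0.95 × 0.05 / n = 0.095 / n, the variance at the assumed rates.
- s0² uses the restricted maximum-likelihood rates when the true difference is −0.10. These are 0.8703 (RTS,S/AS02A) and 0.9703 (control), so s0² = (0.8703 × 0.1297 + 0.9703 × 0.0297) / n = 0.1417 / n.
- z = 1.645 at one-sided 5% and 1.960 at one-sided 2.5%.

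**The plan's own figures first.** For n = 124, s0 = 0.0338 and s1 = 0.0277.

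- At 5%: (0.10 − 1.645 × 0.0338) / 0.0277 = 1.60, power 94.6%. The superseded text said 95%.
- At 2.5%: (0.10 − 1.960 × 0.0338) / 0.0277 = 1.22, power 88.9%. The current text says 89%.

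**Table 7 by the same formula:**

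| n per group | Table 7 | One-sided 5% | One-sided 2.5% | Table 7 minus 2.5% value |
|---|---|---|---|---|
| 112 | 92% | 92.3% | 85.1% | 6.9 |
| 99 | 89% | 88.9% | 79.8% | 9.2 |
| 87 | 85% | 84.6% | 73.7% | 11.3 |

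The column equals the 5% values to rounding.

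**Other formulas at one-sided 2.5%:**

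| Method | n = 124 | 112 | 99 | 87 |
|---|---|---|---|---|
| Asymptotic Farrington-Manning | 88.9 | 85.1 | 79.8 | 73.7 |
| Farrington-Manning score, exact enumeration | 90.1 | 86.8 | 83.5 | 76.5 |
| Unpooled normal, continuity-corrected | 91.3 | 87.8 | 82.7 | 76.4 |
| Corrected Wald, exact enumeration | 90.9 | 87.5 | 83.1 | 76.6 |
| Uncorrected Wald, exact enumeration | 94.5 | 92.1 | 88.8 | 84.9 |
| Unpooled normal, uncorrected | 95.1 | 93.0 | 89.8 | 85.7 |

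Of the methods tried, only the first returns the stated 89% at n = 124.

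**GMT column.** The inputs are SD 0.591 on the log10 scale and a lower limit of 0.5 for the ratio. The noncentrality is log10(2) / (0.591 × √(2/n)) = 3.81, 3.58 and 3.36 for n = 112, 99 and 87. A one-sided 5% t-test, which matches the two-sided 90% interval in the GMT text, gives 98.4/97.3/95.6%, within a point of the stated 99/98/96. At one-sided 2.5% it would be 96.7/94.6/91.6%.

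**The case against.** Three arguments can be made for the plan.

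First, Table 7 could come from a different routine already at 2.5%. Exact enumeration of the uncorrected Wald test at 2.5% gives 92.1/88.8/84.9%, which also rounds to the table's figures. But that test gives 94.5% at n = 124, not 89%, so it contradicts the statement that only the sample size changes. The column also carries no revision mark, while alpha and power in the text do. A column carried over from the 5% calculation fits both facts. On either account, text and table do not come from one calculation.

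Second, the table decides little. The 416 subjects in Cohort 2 follow from 124 per group, the share of children under 24 months and 20% loss. The full-set 89% reproduces. The protocol does not make the seronegative-only analysis the decisive one, and does not say which of the three shares it expects. All of this stands, and it limits the weight of the point.

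Third, a reader might infer that the GMT column is wrong too, since it is not at 2.5%. The documents do not support that. Sections 10.6.2 and 10.7.4 still specify a two-sided 90% interval for the GMT ratio, and the column agrees with that to within a point. Amendment 2's list of changes speaks more generally of a 95% interval for the non-inferiority assessment. Whether this was meant to cover the GMT ratio is a separate question, and not an error in Table 7.

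**Conclusion.** The seroprotection column of Table 7 contradicts the calculation it claims to extend. This follows from the order of the figures alone and needs no choice of formula.

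The size of the error does depend on the formula. With the method that reproduces both the old 95% and the current 89%, the column should read about 85/80/74%, so it is overstated by about 7, 9 and 11 points. Power is then at or below 80% once 80% or fewer of the subjects are seronegative. The exact Farrington-Manning and continuity-corrected variants put the overstatement at roughly 4 to 9 points, but they miss the stated 89%. That the sponsor's software used the asymptotic Farrington-Manning formula is inferred from this match; the protocol does not name the formula.

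It would go too far to infer that Cohort 2 is undersized or that the primary analysis is affected. The error is confined to the stated power of a subset analysis for a secondary objective.

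**What to change.** - Recompute the seroprotection column at one-sided 2.5% with the same PASS routine that gave 89% for 124 per group. Expect about 85/80/74%.
- State the alpha for each column in Table 7, since the two columns rest on different levels.
- Do not claim that the seronegative-only seroprotection analysis keeps at least 85% power.
- Leave the GMT column as it is unless the GMT interval in sections 10.6.2 and 10.7.4 is changed to 95%. If it is, the column becomes about 97/95/92%.

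The cost is a table edit and a less favourable statement of power for the subset. No change to sample size, margin or test follows from it.
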